### **Acupuncture:**

Most common side effects (<5%):

- Very minor bleeding at acupuncture sites
- Bruises at acupuncture sites

- Minor pain or an unfamiliar sensation at acupuncture sites (local or radiating)

Less common side effects (<1%):

- Local allergic reaction (urticaria)
- Drowsiness, sleep disturbances (insomnia)
- Anxiety, nervousness
- Fainting, dizziness, nausea, vomiting (vasovagal reaction)

Rare but more serious side effects (<0.1%):

- Local skin infection

Severity will be graded as “serious” or non-serious.” Serious AEs are those that require hospitalization, lead to death or disability or require urgent medical attention to prevent death or disability. The intensity of non-serious AEs will be graded as mild, moderate or severe.

Causality will be assessed as follows. The AE will be described as "Probable" if all of the following apply: there is a rational relationship between the occurrence of the AE and the time of treatment; the AE has already been described as an AE of acupuncture or could reasonably be anticipated to be an acupuncture AE; regression or disappearance of the AE (unless permanent) after discontinuation of treatment or dose reduction; AE cannot plausibly be explained in terms of other causal factors. The AE will be described as "Possible" if all of the following apply: there is a rational relationship to the time of treatment administration; the AE has already been described as an AE of acupuncture; the AE could be explained by other factors. The AE will be described as "Improbable" if the following apply: there is no rational relationship to the time of treatment administration; the AE has not been reported so far as a side effect of treatment and cannot reasonably be expected as an acupuncture side-effect and any of the following: non-permanent AE persists after discontinuation of the treatment or dose reduction; repeated exposure does not lead to reappearance of the AE; AE could be explained by numerous other factors. The AE will be described as "No relationship" if all of the following apply: there is no rational relationship to the time of treatment administration; AE is evidently caused by other factors, e.g. symptom of a concomitant disease. The AE will be described as "Unable to evaluate" if the amount and content of data do not permit a judgment of the relationship to the treatment.

Quantitative Sensory Testing (QST): QST is not invasive and associated with no known risk.

Controlled Pain Modulation: CPM is not invasive and associated with no known risk.

Risk of psychological distress: Some of the questions in the questionnaire may elicit distress for some patients. If a patient demonstrates clinically significant distress, s/he will be referred to the appropriate clinical/psychosocial services. An appropriate referral will be made if anxiety (7 items) or depression (7 items) scores for the HADS is greater than 10 as 11-21 indicates clinically significant depression/anxiety.

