| Study Allocation Belief                                                                                          |   |   |   | X |
| Pain Medication List                                                                                          | X | X | X | X |
| Safety Assessment                                                                                                | X | X | X |   |
| Quantitative Sensory Testing (QST)                                                                               | X |   | X | X |
| Controlled Pain Modulation (CPM)                                                                                 | X |   | X | X |

1. In the case of any missed sessions during the study, the testing, questionnaires and other assessments should occur in the same week as planned. In the case of early discontinuation of treatment, all attempts will be made to collect the questionnaires until the end of the study.
2. ECOG Performance Status will be assessed  $\leq 28$  days before the consent.
3. The medication lists will include both prescription and non-prescription pain medication.
4. Patients will be monitored for side effects at each acupuncture and sham acupuncture session .
5. This will be performed by an IMS research study assistant who will go through training before the initiation of the study. A window of + 1 week applies to the baseline assessments, and a window of +/- 3 days applies to week 8 and week 12 assessments.
6. Can be performed over the phone.

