and left index fingers and both the left and right big toes. We will ask subjects to indicate when they feel the vibration stimulus for the first time (perception threshold) and when this stimulus disappears again (disappearance threshold). The average of three-paired measurements is considered to be the VT at the location investigated. The thermal threshold will be measured by the TSA-II system, which is a thermal sensory analyzer, providing for evaluation of cool sensation, warm sensation, heat-pain, and cold-pain thresholds. Its temperature (stimulation) range is 0 to 50°C, with a programmable stimulation rate of up to 8°C per second. Thermal thresholds will be assessed by the method of limits. First, the thermode will be attached and the skin will be allowed to adapt to a temperature of 32°C. For the sensory threshold assessment, the thermode will be warmed or cooled at a slow rate (1°C/s) until the subject perceives the first warm or cold pain sensation. For the heat-pain and cold-pain thresholds, we will increase/decrease the temperature at a rate of 2°C/s until the moment that the subject indicates the transition of the warm/cold sensation into a painful sensation. We will repeat each test three times and average the results to obtain the threshold value.

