### **Controlled Pain Modulation (CPM)**

At baseline, at the end of the 8-week acupuncture treatment, and at week 12, all patients will undergo CPM testing to determine the effectiveness of their descending inhibitory pathway. We will use the above-mentioned TSA-II system to administer tonic heat pain as the “test stimulus” in the CPM protocol. Hand immersion in the water bath apparatus, a temperature controlled container, will serve as a conditioning stimulus. We will use Heto water bath for hand immersion as the conditioning stimulus. We will measure CPM using the parallel paradigm in which two identical noxious ‘test stimuli’ will be delivered before and simultaneously with a noxious ‘conditioning stimulus.’ The test stimulus is first applied to the dominant forearm to reach a pain rating of greater than 60 on a numeric pain scale of 0-100. Patients will be asked to rate the level of pain intensity of the test stimulus (pain60 temperature) every 10 seconds (overall 4 pain reports). After a 15-minute break, the non-dominant hand will be immersed in the cold water bath up to the wrist at 10°C for 60 seconds. During the last 30 seconds of this immersion, the test stimulus will be repeated, and the patient will again rate the level of pain intensity experienced. The CPM effect is calculated as the difference (last minus first) in the average pain scores of the 2 test stimuli. A negative value indicates efficient CPM. This paradigm of conditioned pain modulation is routinely used in pain research.

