## **11.0 TOXICITIES/SIDE EFFECTS**

Patients will be monitored for side effects at each visit. Only adverse effects related to the administration of acupuncture will be collected each week by the acupuncturist or research study assistant.

Acupuncture is a generally safe treatment modality when performed by qualified practitioners. No serious adverse events were reported in our pilot study.

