### **17.2 Serious Adverse Event (SAE) Reporting**

An adverse event is considered serious if it results in ANY of the following outcomes:

- Death
- A life-threatening adverse event
- An adverse event that results in inpatient hospitalization or prolongation of existing hospitalization
- A persistent or significant incapacity or substantial disruption of the ability to conduct normal life functions
- A congenital anomaly/birth defect
- Important Medical Events (IME) that may not result in death, be life threatening, or require hospitalization may be considered serious when, based upon medical judgment, they may jeopardize the patient or subject and may require medical or surgical intervention to prevent one of the outcomes listed in this definition

Note: Hospital admission for a planned procedure/disease treatment is not considered an SAE.

SAE reporting is required as soon as the participant signs consent. SAE reporting is required for 30-days after the participant's last investigational treatment or intervention. Any events that occur after the 30-day period and that are at least possibly related to protocol treatment must be reported.

If an SAE requires submission to the IRB office per IRB SOP RR-408 'Reporting of Serious Adverse Events', the SAE report must be sent to the IRB within 5 calendar days of the event. SAE's classified as unrelated to the study intervention (per section 11.0) will not be

considered reportable to the IRB and will not have a corresponding Clinical Research Database (CRDB) SAE report generated). The IRB requires a Clinical Research Database (CRDB) SAE report be submitted electronically to the SAE Office as follows:

For IND/IDE trials: Reports that include a Grade 5 SAE should be sent to [[contact]](mailto:[contact]). All other reports should be sent to [[contact]](mailto:[contact]).

For all other trials: Reports that include a Grade 5 SAE should be sent to [[contact]](mailto:[contact]). All other reports should be sent to [[contact]](mailto:[contact]).

The report should contain the following information:

Fields populated from CRDB:

- Subject's initials
- Medical record number
- Disease/histology (if applicable)
- Protocol number and title

Data needing to be entered:

- The date the adverse event occurred
- The adverse event
- The grade of the event
- Relationship of the adverse event to the treatment (drug, device, or intervention)
- If the AE was expected
- The severity of the AE
- The intervention

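### The protocol says QST and CPM carry no known risk and has no provision for collecting their non-serious effects, although both apply deliberately painful heat and cold in all three arms

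*Protocol*

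**What the plan says.** **Risk statements.** Section 11.0 of the protocol says "QST is not invasive and associated with no known risk" and, in the next entry, "Controlled Pain Modulation: CPM is not invasive and associated with no known risk".

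**What the tests do.** Section 8.0 (Quantitative Sensory Testing) ramps a thermode from 32°C at 2°C/s until the patient reports that warmth or cold has become painful, with each test done three times. Of the device it says "Its temperature (stimulation) range is 0 to 50°C". Section 8.0 (Controlled Pain Modulation) sets forearm heat to a pain rating above 60 out of 100 and adds a cold stimulus: "the non-dominant hand will be immersed in the cold water bath up to the wrist at 10°C for 60 seconds". It calls both the test and the conditioning stimulus noxious. Sections 4.2 and 8.0 and Table 2 give QST and CPM to all three arms at baseline, week 8 and week 12.

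**What is collected.** Section 11.0 opens with "Patients will be monitored for side effects at each visit" and continues: "Only adverse effects related to the administration of acupuncture will be collected each week by the acupuncturist or research study assistant". Section 9.0 repeats the restriction to acupuncture and places collection before and after each treatment. Footnote 4 of Table 2 explains the Safety Assessment row: "Patients will be monitored for side effects at each acupuncture and sham acupuncture session". That row is marked at baseline, week 4 and week 8, but not at week 12.

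**Serious events.** Section 17.2 requires reporting from consent onwards, with no restriction by arm. It then exempts from IRB and CRDB reporting "SAE's classified as unrelated to the study intervention (per section 11.0").

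**The concern.** The risk statements sit badly with the protocol's own description of the tests, and the collection rule leaves effects of the tests out of the data.

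Usual care patients receive no study treatment up to week 12, so QST and CPM are the only physical procedures the study imposes on them beyond height and weight. If the collection sentence is followed as written, a skin reaction, a faint or lasting discomfort after a test has no defined place in the record unless it is serious. The pilot exists to inform a definitive trial. That trial would inherit a statement that the tests are free of risk without any data collected to check it.

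**Working it through.** The protocol states no figure on this point. The check is a comparison of the passages and a count of sessions.

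**1. Risk statement against test description.** Section 11.0 lists minor needle pain as a side effect of acupuncture and distress from questionnaire items as a risk. By that standard, pain induced on purpose at a rating above 60/100 is a foreseeable effect and belongs in the list. Nothing is listed for it. The risk text in Section 17.0 names acupuncture and questionnaire distress, but neither test.

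**2. Monitoring against collection.** Monitoring at each visit, read alone, could cover a QST/CPM visit. The next sentence uses the word *only* and confines collection to effects of acupuncture. So an effect of a test may be noticed, but it has no instruction to be recorded.

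**3. Sessions affected.** The inputs are 75 patients, 25 per arm (Section 4.1), and 3 test visits (Table 2). Full attendance is assumed, so the counts are upper limits and apply to each test separately.

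- All sessions: 75 × 3 = 225.
- Usual care, which has no treatment sessions for footnote 4 to cover: 25 × 3 = 75.
- Week 12, all arms, with no Safety Assessment mark: 75 × 1 = 75.
- Usual care or week 12, counting the overlap once: 75 + 75 − 25 = 125 of 225 (56%).
- Remaining sessions, at baseline and week 8 in the two needling arms: 50 × 2 = 100. The calendar has a Safety Assessment mark here, but the collection sentence still limits its content to acupuncture.

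Per patient and tested site, the plan has 3 repeats × 3 visits = 9 heat-pain ramps and 9 cold-pain ramps. CPM at each visit adds two heat stimuli and one immersion.

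**4. The route for a serious event.** The causality scale in Section 11.0 was read for a hypothetical serious event caused by a test.

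- *Probable* needs a link in time to treatment and an event that is known or could be anticipated as an effect of acupuncture.
- *Possible* needs the link in time and an event already described for acupuncture.
- *No relationship* needs no link in time to treatment and an event evidently due to other factors.

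In usual care no treatment is given, so the first two categories are hard to reach and *No relationship* fits readily. In the needling arms the result depends on timing and event type: fainting, for example, is on the acupuncture list. An event judged unrelated under this scale then meets the exemption in Section 17.2.

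**The case against.** Much of the case on the other side is right.

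- **Harms are not simply unrecorded.** Section 11.0 does state monitoring at each visit. Safety Assessment is marked at baseline and week 8, and the row itself names no arm. Section 17.2 covers serious events from consent. A reader might infer that nothing would ever be recorded, but the text does not support that. The gap is in collecting non-serious effects.
- **Loss of a serious event is possible, not certain.** Section 17.2 does not define the study intervention as acupuncture alone. The scale has an *Unable to evaluate* category, and the report form asks whether the event is an unanticipated problem.
- **No injury risk is shown.** Brief pain that the patient ends by reporting it is the measurement itself. Section 8.0 describes the CPM paradigm as routine in pain research, and the documents give no injury rate or case for either test.
- **The tempting exposure argument fails.** A reader might infer that patients with numbness would be heated to 50°C, since at 2°C/s the device limits are reached in (50 − 32)/2 = 9 s or (32 − 0)/2 = 16 s. But 50°C is a device limit, not a planned temperature, and the text does not say that a ramp runs to it. Numbness is one of three qualifying symptoms. Section 3.0 also lists heightened pain sensitivity, which could end a ramp sooner. The CPM heat is set by the patient's own rating on the forearm, and the thermode site for the thermal thresholds is not stated.
- **Consent pages are not available,** so what patients are told about discomfort cannot be judged.

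What remains is that the collection sentence excludes effects of the tests, no treatment session brings usual care patients into safety collection, week 12 has no safety mark, and the causality scale refers only to acupuncture.

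**Conclusion.** The point holds as an inconsistency and a collection gap. Two risk statements do not match the painful procedures that the protocol describes. Non-serious effects of QST and CPM have no collection provision at any of up to 225 sessions of each test. At up to 125 of these (usual care or week 12) even the safety assessment for acupuncture does not clearly apply. A serious event caused by a test may be classed as unrelated and go unreported to the IRB and CRDB, most readily in usual care.

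This rests on full attendance for the counts, and on reading the *only* sentence in Section 11.0 as the operative collection rule. It does not rest on any assumed rate of injury, and none can be derived from the documents. The primary endpoint and its analysis are not affected. The point should be fixed, because the gain is in participant safety and the change is small.

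**What to change.** 1. In Section 11.0, reword the two risk statements so that they acknowledge the pain and discomfort that QST and CPM induce, consistent with Section 8.0. Bring the risk text in Section 17.0 into line.
2. Extend the collection sentence in Section 11.0 to effects related to acupuncture, sham acupuncture, QST or CPM. Record them at each QST/CPM visit in all three arms. Align Section 9.0 and footnote 4 of Table 2 with this, and mark Safety Assessment at week 12.
3. In Sections 11.0 and 17.2, judge relatedness to the study intervention or a study procedure, so that a serious event caused by a test is not exempted by the wording of the scale.

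The investigators should reconcile Section 8.0 (QST and CPM), Section 11.0, Table 2 with footnote 4, and Section 17.2. No stimulus limit is proposed here.

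The cost is a wording amendment and one short form at three visits that already take place, with a research study assistant conducting the tests. No extra visit or procedure is needed.

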## **12.0 CRITERIA FOR THERAPEUTIC RESPONSE/OUTCOME ASSESSMENT**

The primary endpoint will be measured by NRS of the most bothersome CIPN symptom and measured at time of consent (baseline) and at 8 weeks, after the final acupuncture session for the acupuncture or sham acupuncture arms and at baseline and after 8 weeks of usual care for patients randomized to the usual care arm. Secondary endpoints will be measured by the FACT/GOG-NTx, NPS, NCI-CTC 4.0, ISI, HADS, BFI, TES, QST, and CPM. Additionally, NRS will be assessed as a secondary aim at baseline, 4 weeks, and 12 weeks for all arms. All non-NRS secondary endpoints will be assessed at baseline, 8 weeks and 12 weeks. The NPS and FACT-GOG/NTX will also be assessed at 4 weeks.

All patients enrolled in the study who completed acupuncture or sham acupuncture will be included in the analyses, and any patients who withdraws from the study or who is lost to followup will be described.

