### **13.0 CRITERIA FOR REMOVAL FROM STUDY**

Patients will be removed from the study if they experience unacceptable adverse events from acupuncture. If at any time the primary oncologist believes it is in the best interest of the participant to be withdrawn from the study, the participant will be withdrawn. Study subjects also may elect to withdraw from the study. Patients who withdraw will be asked for their reasons defined as: acupuncture treatment inconvenience; belief that treatment is ineffective; data collection inconvenience; medical reasons; or other. Patients who discontinue participation in the study will be asked if they are willing to provide follow-up data or whether they wish to withdraw completely.

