neuropathy we will use linear regression to assess the association between NRS and TT, VT, and THT at baseline, and the association between change in NRS with change in TT, VT, and THT. For the mechanistic studies, we will use an interaction term between baseline CPM and real acupuncture to predict NRS at 8 weeks:  $NRS_8 = \beta_1 NRS_0 + \beta_2 CPM_0 + \beta_3 \text{Real Acupuncture} + \beta_4 CPM_0 \times \text{Real Acupuncture} + c$ . We will also test acupuncture-induced changes in CPM as  $CPM_8 = \beta_1 CPM_0 + \beta_2 \text{Real Acupuncture} + \beta_3 \text{Any Acupuncture} + c$ . We will also explore the relationship between treatment expectancy and response adjusting for baseline CIPN and treatment arm using multivariable linear regression comparing acupuncture versus sham acupuncture:  $NRS_8 = \beta_1 NRS_0 + \beta_2 \text{Real Acupuncture} + \beta_3 \text{Treatment Expectancy} + c$ . We will also estimate the change in mean HADS, BFI and ISI scores from baseline to 8 and 12 weeks along with a 95% confidence intervals, separately. We will also estimate the proportion of patients with a dose reduction and the proportion of patients who experience a dose escalation of neuropathy medication during the course of the 12 weeks along with an upper 90% confidence interval. All analyses will be by intent to treat, with participants analyzed according to allocation irrespective of treatment actually received. We will use multiple imputation, including 4 week outcome, for missing data at 8 weeks. Patients with 4 and 8 week outcomes are missing, they will not be included in the analysis.

For a trial with 25 patients per group, and an anticipated correlation between baseline and follow-up measures of 0.5, we will be able to calculate the upper bound of a one-sided, 90% confidence interval for the coefficients of any treatment and real acupuncture to approximately 0.35 standard deviations.

Last year, 935 solid tumor survivors had a diagnosis of persistent CIPN 3 months after chemotherapy completion. A recent study showed that among breast cancer survivors 28% reported moderate to severe CIPN 3 months after chemotherapy completion. Therefore, we anticipate 262 patients are eligible per year for our proposed study. Assuming at least a 15% enrollment rate of the eligible patients the estimated accrual is 3-4 patients per month, the estimated accrual period is between 19 and 25 months in order to identify 75 eligible patients.

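### Section 12 limits the analyses to patients who completed acupuncture or sham, while Section 14 analyses everyone as allocated; the completers rule can bias the contrasts with usual care and should be brought into line

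*Protocol*

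**What the plan says.** Section 12 (outcome assessment) defines who is analysed: "All patients enrolled in the study who completed acupuncture or sham acupuncture will be included in the analyses". The same sentence goes on to say that "any patients who withdraws from the study or who is lost to followup will be described". It does not define completion and does not mention usual care patients.

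Section 14 (biostatistics) gives a different rule: "All analyses will be by intent to treat, with participants analyzed according to allocation irrespective of treatment actually received". For missing outcomes it adds: "We will use multiple imputation, including 4 week outcome, for missing data at 8 weeks". It then makes an exception: "Patients with 4 and 8 week outcomes are missing, they will not be included in the analysis". The grammar is faulty, but the sense is that patients missing both outcomes are left out.

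Two other places provide for follow-up after stopping. Footnote 1 to the study calendar (Table 2) says: "In the case of early discontinuation of treatment, all attempts will be made to collect the questionnaires until the end of the study". Section 13 says: "Patients who discontinue participation in the study will be asked if they are willing to provide follow-up data".

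**The concern.** The protocol gives two rules for who enters the primary analysis, and they disagree on patients who stop treatment early but still report a week 8 NRS. An analyst could follow either rule and claim to follow the protocol, so the choice could be made after the data are seen.

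The Section 12 rule is the harmful one. Completing treatment happens after randomisation and can happen in only two of the three arms. Section 13 lists a belief that treatment is ineffective among the reasons for withdrawal, and makes unacceptable adverse events from acupuncture a ground for removal. Stopping may therefore be related to outcome. If so, a completers rule takes poorer responders out of the two needled arms and leaves usual care untouched.

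The completion rule is also hard to apply. Section 4.2 says that missed sessions are not made up without approval, so the status of a patient with nine of ten sessions is open.

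The stakes are those of a pilot. Section 14 will plan the next trial if the confidence interval for the acupuncture effect includes clinically relevant values, and it will take the SD and the baseline/follow-up correlation from these data. Selecting patients can distort all of these.

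**Working it through.** **The two rules side by side.** Take a patient randomised to acupuncture who stops at session 5 and completes the week 8 questionnaire. Section 14 analyses this patient in the acupuncture arm, irrespective of treatment received. Section 12 includes completers and describes withdrawals, so its natural reading leaves the patient out. The Table 2 footnote and Section 13 collect data from such patients, which fits Section 14 and would be wasted under Section 12.

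**The plan's own precision figure.** Section 14 gives 25 per arm, correlation r = 0.5 and a one-sided 90% bound at about 0.35 SD. The ANCOVA half-width is z(0.90) × √[(1 − r²) × 2/n] = 1.2816 × √(0.75 × 2/25) = 0.314 SD (0.317 with a t quantile). The stated 0.35 is therefore not reproduced at n = 25 and is somewhat conservative. With 20 per arm the formula gives 0.351, but the protocol states no such loss. This does not decide the present point; it supplies a yardstick.

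**Bias from the completers rule.** The documents give no dropout rate and no outcome difference for patients who stop, so these are assumptions:

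- A share d of each needled arm is excluded, and nobody in usual care.
- Exclusion falls on the upper tail of a latent variable that correlates ρ = 0.3 or 0.5 with the week 8 score, so worse scores are more likely to be excluded.
- r = 0.5, as in Section 14, and there is no true treatment effect.

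After baseline adjustment, the spurious benefit against usual care is approximately ρ(1 − r²) × φ(c)/(1 − d), with c = Φ⁻¹(1 − d). For d = 0.10, φ(c)/(1 − d) = 0.1755/0.90 = 0.195, and 0.3 × 0.75 × 0.195 = 0.044 SD. A simulation with 400,000 patients per arm, using the Section 14 treatment coding without the symptom terms, agrees. The last two columns show the size of its any-acupuncture coefficient.

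| d | φ(c)/(1 − d) | Formula, ρ = 0.3 | Formula, ρ = 0.5 | Simulated, ρ = 0.3 | Simulated, ρ = 0.5 |
|---|---|---|---|---|---|
| 10% | 0.195 | 0.044 | 0.073 | 0.043 | 0.073 |
| 20% | 0.2800/0.80 = 0.350 | 0.079 | 0.131 | 0.082 | 0.137 |
| 30% | 0.3477/0.70 = 0.497 | 0.112 | 0.186 | 0.116 | 0.186 |

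At 10-20% exclusion the shift is about 0.04-0.14 SD. The upper value is 0.14/0.35 = 40% of the precision margin that the protocol quotes.

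**Acupuncture versus sham.** With equal exclusion the simulated shift is within 0.003 SD of zero. With 10% excluded in acupuncture and 20% in sham it is 0.038 SD (ρ = 0.3) to 0.060 SD (ρ = 0.5), against acupuncture. The rule also costs precision here: the half-width rises from 0.314 to 0.331, 0.351 and 0.375 SD at 10%, 20% and 30% exclusion in both arms.

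**Patients missing both weeks 4 and 8.** Under the same model, equal loss of 5-20% in all arms gives a bias of about zero. Loss of 15% in usual care against 5% in the needled arms gives about 0.04-0.06 SD, against treatment. Table 2 schedules NRS, NPS and FACT/GOG-Ntx at week 12 as well, so a patient without weeks 4 and 8 may still have a usable later score that the rule discards.

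**The case against.** The strongest reply is that the documents largely settle the matter. The statistical section applies intent to treat to all analyses, the follow-up provisions match it, and Section 12 holds one stray sentence that never says that only completers are analysed. This is also a pilot, and the contrast intended for the definitive trial, acupuncture versus sham, is little affected if completion is equal. Much of this stands: it shows which way to reconcile the two sections and limits the size of the problem. It does not remove the contradiction. Setting those who are included against those who are described has no other sensible reading, and the contrasts with usual care belong to the primary objective.

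A reader might infer more than the text supports:

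- **Three rival analysis sets.** There are two conflicting rules. The exclusion for missing weeks 4 and 8 is a missing-data restriction within the Section 14 approach and does not select on treatment received.
- **That exclusion breaks the randomised comparison.** It biases the contrast only if such loss differs by arm and is related to outcome.
- **Usual care is dropped altogether.** Section 12 itself measures the primary endpoint after 8 weeks of usual care, and Section 14 codes that arm in the primary model.
- **Week 12 is barred from the imputation.** Section 14 says that the week 4 outcome is included, which does not exclude other variables. Handling of endpoints without a week 4 visit may properly sit in an analysis plan that is not shown.
- **The net duloxetine effect in Section 3 (1.06 − 0.34 = 0.72 points) is a yardstick.** It is a placebo contrast, whereas the bias here concerns usual care.

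It is also fair to say that, for patients with no post-baseline data, imputing from arm, baseline and symptom type adds essentially no information on the treatment effect.

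**Conclusion.** The point holds as a contradiction between Sections 12 and 14 over who enters the primary analysis, and the Section 12 rule is wrong as written. Following it would condition on an event that cannot occur in usual care. It would favour treatment against usual care by about 0.04-0.14 SD if 10-20% of the needled arms were excluded and those patients tended to do worse. If stopping is unrelated to outcome, this bias disappears. Dropout rates and outcome differences are assumed throughout, so the direction is better supported than the size.

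The exclusion of patients missing both weeks 4 and 8 is a lesser matter. It makes the intent-to-treat label inexact and can discard patients with a week 12 score. How many there would be cannot be judged from the documents.

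**What to change.** 1. Replace the Section 12 sentence with a statement that all randomised patients in all three arms are analysed as allocated, as in Section 14. Any completers analysis should be a sensitivity analysis only, with completion defined in advance.
2. In Section 14, add the week 12 score to the imputation model for NRS, NPS and FACT/GOG-Ntx, and keep patients who have it but lack weeks 4 and 8.
3. If the exclusion stays for patients with no post-baseline data, call it an exception to full intent to treat, report the counts by arm, and add a sensitivity analysis that keeps all randomised patients.

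The cost is protocol wording, a slightly larger imputation model and, if the exclusion stays, one more sensitivity analysis. No new data or patients are needed.
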